## Abstract

**Background:**

Repetitive transcranial magnetic stimulation (rTMS) is a technique for stimulating brain activity using a transient magnetic field to induce an electrical current in the brain producing depolarization of focal groups of brain cells. TMS is a protocol approved by the U.S. Food and Drug Administration in routine clinical practice as a treatment for depression. A major limitation of rTMS is the large amount of time taken for a standard protocol (38 min a day for 20–30 working days). The optimal type and duration of TMS are still uncertain, as is the optimal strategy for continuing or changing the type of rTMS if there is a poor initial response.

**Objectives:**

The trial aims to assess whether a 1-week compressed course of left dorsolateral prefrontal (L DLPFC) 5 Hz accelerated rTMS (aTMS) treatment is as effective as an established 4-week course of non-accelerated rTMS and if additional 5 Hz L DLPFC aTMS treatments will be efficacious in non-responders as compared to 1 Hz right DLPFC aTMS treatment.

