## Methods

### Objectives

The primary aim of this study is to test the symptomatic efficacy of aTMS trial protocol. The 2nd aim is to compare the symptomatic efficacy of the early-start aTMS treatment group and delayed-start aTMS treatment group in patients with a DSM 5 Major Depressive Episode. The exploratory aim is to test whether the non-responders to a 1-week course of aTMS will have a higher chance of response to a change in aTMS than repeated the same aTMS modality (from 5 Hz L DLPFC aTMS to 1 Hz R DLPFC aTMS).

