### Hypothesis

We hypothesize that accelerated 5 Hz L DLPFC rTMS is effective for the treatment of depressive symptoms with regard to reducing the MADRS scores from baseline to end week 3 in the overall study sample.

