#### Exclusion criteria

DSM-5 psychotic disorder.Drug or alcohol abuse or dependence (preceding 3 months).Inadequate response to ECT (current episode of depression).Rapid clinical response required, e.g., high suicide risk.Significant neurological disorder, which may pose increased risks with TMS, e.g., epilepsy.Metal in the cranium, skull defects, pacemaker, cochlear implant, medication pump, or other electronic devices.Pregnancy.

The following clinical data will be collected at baseline: age, gender, ethnicity, duration of index episode, type of depression (unipolar/bipolar, melancholic/non-melancholic), number of failed antidepressant treatments, number of previous depressive episodes, age at the first depressive episode, and family history of affective disorder will be noted. Full informed written consent will be obtained from all participants.

#### Randomization at phase 1

In phase 1, subjects were randomly assigned either to the early-start group (immediate active treatment) or the delayed-start group (no TMS treatment for one week followed by active treatment, see Fig. 1). Randomization was done using a random sequence number generator.

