**Fig. 1 Fig1:**
[figure not shown]
Graphical display of the delayed-start design

#### Treatment at phase 1

During the active treatment phase, all participants will receive 5 Hz aTMS over the L DLPFC, 4 treatment sessions a day (each session consisting of 3000 pulses for 12 000 pulses a day), every weekday for 1 week. We will use a Magventure X100 TMS Therapy System to conduct TMS stimulation. The first treatment session will take approximately 3 h as participants will also be familiarized with the TMS equipment/procedure and resting motor threshold (RMT) will be determined at this session. We use visual assessment of the respective dorsal interosseous muscle contraction (5 out of 10 stimulations) induced by TMS to determine RMT. Subsequent sessions are expected to last about 2 h each. Stimulation will be applied at the left prefrontal cortex (F3 according to the EEG 10/20 system). L DLPFC aTMS will be delivered at 120% of the RMT, as measured at the initial session. Each TMS train will last for 8 s and have a 12-s intertrain interval. Each session will have 75 trains. Thus, it will be taking about 25 min for each session which includes setting up time.

aTMS will be conducted in a room with facilities for managing seizures. Participants and experimenters will be offered earplugs during the sessions. Sessions will be done by staff trained and credentialed in TMS according to the Singapore College of Psychiatrists guidelines for TMS. Staff will also be trained for initial seizure management.

Patients in the delayed-start group will be treated as usual during the delayed week and will receive aTMS treatment at 1 week after recruitment. Subjects in the delayed-start group and early-start group will both be monitored with weekly outcome assessments. Subjects in the delayed start arm who still fulfill the criteria for study entry at the end of the delayed start phase will continue on to the active treatment phase of the study. No change in psychiatric medication will be allowed during this period.

#### Evaluation of clinical response at phase 1

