Subjects who have not remitted from the 1st active treatment will enter phase 2 treatment. The second randomization will be stratified into three groups based on whether the participant showed <25% improvement in MADRS scores, between 25% and ≤50% improvement in MADRS scores or >50% improvement in MADRS scores. After that, participants in each group will be randomized (in permuted blocks) to either L DLPFC or R DLPFC treatment. The purpose of patient stratification basing on MADRS score before randomization is a method of permuted block randomization, which is a way to randomly allocate a participant to a treatment group, while maintaining a balance across treatment groups. Each “block” has a specified number of randomly ordered treatment assignments depending on the response to the initial aTMS treatment. Randomization will be generated by study team members who are not involved in the treatment. Treatment assignment is determined by treating doctors. Patients, their caregivers, nurse clinicians, and doctors who do the treatment and outcome assessments will be blinded to the randomization.

#### Treatment at phase 2

Subjects who entered phase 2 will receive another 1 week of 5 Hz L DLPFC aTMS (same protocol as above) or aTMS consisting of right DLPFC at 1Hz, 4 treatment sessions a day (each session consisting of 3000 pulses for 12000 pulses a day), every weekday for 1 week. These patients will also be followed up with weekly assessments for 2 weeks after the end of the second round of aTMS. Therefore, participants who receive a total of 1 week of daily aTMS would have received 60000 pulses while those who received a total of 2 weeks of daily aTMS would have received 120000 pulses.

We will use the Magventure X100 to carry out low-frequency R DLPFC. 1 Hz R DLPFC aTMS will take about 4 h a day. Stimulation will be delivered at the right prefrontal cortex (F4 according to the EEG 10/20 system). R DLPFC aTMS will be delivered at 120% of the RMT, as measured at the initial session. Each session will have 300 trains which is equivalent to a consensus protocol of delivering 3000 pulses per session over the L DLPFC [46].

#### Evaluation of clinical response at phase 2

Similar to the outcome assessment during phase 1, mood improvement and subject QoL will be assessed every week during acute treatment by a trained rater (blinded to treatment allocation) using the MADRS scale until 2 weeks after the initiation of 2nd round of treatment.

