## Conclusions

In summary, this trial is expected to clarify the clinical advantages of compressed TMS treatment vs. the standard treatment protocol of TMS. If this trial reveals the appropriate protocol of aTMS, this result can be published to enhance local and international TMS treatment guidelines.

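### The Abstract asks whether 1-week aTMS matches a 4-week standard rTMS course, but no patient is assigned standard rTMS and only change from baseline is tested

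*Protocol article*

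**What the plan says.** All references are to the protocol article.

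- **Abstract, Objectives:** the trial is to assess whether 1 week of 5 Hz left-sided aTMS "is as effective as an established 4-week course of non-accelerated rTMS". A second clause asks about left versus right aTMS in non-responders.
- **Conclusions:** "this trial is expected to clarify the clinical advantages of compressed TMS treatment vs. the standard treatment protocol of TMS".
- **Methods, Objectives:** "The primary aim of this study is to test the symptomatic efficacy of aTMS trial protocol". The second aim is early versus delayed start. The exploratory aim is a change of modality versus repeating the same one in non-responders. Standard rTMS is not mentioned.
- **Hypothesis:** the 5 Hz course is effective with regard to "reducing the MADRS scores from baseline to end week 3 in the overall study sample".
- **Randomization at phase 1:** patients go "either to the early-start group (immediate active treatment) or the delayed-start group (no TMS treatment for one week followed by active treatment".
- **Treatment at phase 1:** "During the active treatment phase, all participants will receive 5 Hz aTMS over the L DLPFC".
- **Randomization at phase 2:** "participants in each group will be randomized (in permuted blocks) to either L DLPFC or R DLPFC treatment". Under Treatment at phase 2, both options are accelerated courses.
- **Statistical analysis:** paired t tests of change from baseline, followed by repeated-measures ANOVA, all two-tailed.
- **Sample size calculation:** the study is powered for the fall from baseline to end of week 3 in the whole sample. The planning values are the centre's own results with standard rTMS.

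**The concern.** Whether one treatment is as effective as another is an equivalence or non-inferiority question. It needs patients on the other treatment, or at least a specified external benchmark, and a margin that says how much worse would still be acceptable. The document has none of these. The two phase 1 arms differ by a one-week delay before the same accelerated treatment, and the two phase 2 arms are both accelerated.

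This is not a detail that a statistical analysis plan could supply, because no analysis plan can create a comparator that was never assigned.

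What is at stake is the reading of a positive result. The primary test rejects zero change. A course that delivers well under half of the standard benefit could pass it, and a reader who has seen only the Abstract could take that as parity with the 4-week course.

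**Working it through.** **1. Is there a comparator anywhere?** Phase 1 compares early with delayed start of the same 5 Hz left-sided aTMS. Phase 2 compares left-sided with right-sided aTMS. Standard rTMS is assigned in neither. The Methods aims, hypothesis, analysis and power statement contain no margin and no test against a fixed value.

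**2. Reproducing the plan's own figure.** Inputs from Sample size calculation: baseline 25.4 (SD 7.3), week 4 of standard rTMS 14.1 (SD 10.7), 12 participants, 95% power.

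- Mean fall = 25.4 − 14.1 = 11.3 points.
- SD of change = √(7.3² + 10.7² − 2·r·7.3·10.7), where r is the baseline-to-follow-up correlation. The document does not give r.
- With r = 0.5 assumed, the SD of change is 9.47. A two-sided paired t test at alpha 0.05 then needs n = 12 (power 96.3%), which matches the stated 12. At alpha 0.05, r = 0 would need 20 and r = 0.6 would need 10.
- The alpha is printed as 0.5. That value gives n of 3 to 8 for r = 0 to 0.7, so 0.05 appears to be meant. This is a separate matter.

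The stated sample size is therefore consistent with a one-sample test of change against zero.

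**3. How small a fall passes that test?** The just-significant observed mean fall is t(0.975, n−1) × SD of change / √n. The two sample sizes are the full 60 and the completers left after the planned 60% dropout, 60 × (1 − 0.6) = 24.

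| Assumed r | SD of change | n = 60 | n = 24 |
|---|---|---|---|
| 0 | 12.95 | 3.35 | 5.47 |
| 0.3 | 11.00 | 2.84 | 4.64 |
| 0.5 | 9.47 | 2.45 | 4.00 |
| 0.7 | 7.64 | 1.97 | 3.23 |

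The largest entry, 5.47, is 5.47 / 11.3 = 48% of the centre's fall with standard rTMS. The smallest, 1.97, is 17%.

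**4. Could the 60 patients have supported the comparison?** This step is illustrative only, because the document gives no margin. For two equal arms, n per arm = 2 × SD² × (1.960 + 0.842)² / margin² (one-sided 0.025, 80% power, no true difference). With SD 10.7, an assumed margin of 3 points gives 200 per arm and 4 points gives 113. The finding does not depend on these figures. They show why the remedy lies in the wording.

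**The case against.** The strongest reply is that the operative text is consistent on this point. The Methods aims, hypothesis, analysis and power statement all describe change from baseline, and none claims parity. The fault sits in one clause of the Abstract with a loose echo in the Conclusions, and correcting it alters no randomisation, analysis or sample-size step. That is right, and it makes this a correction of wording. It does not remove the fault, because the Abstract states an aim that the trial cannot meet.

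Four stronger readings are tempting, and the text does not support them:

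- **That every patient receives aTMS.** The plan says "Subjects in the delayed start arm who still fulfill the criteria for study entry at the end of the delayed start phase will continue", so delayed-start patients who no longer qualify do not go on to active treatment. What holds is that no patient is assigned standard rTMS.
- **That a significant fall would be presented as parity.** No section says so. The Abstract's Discussion ties dissemination to the protocol proving effective, not equivalent. Only the possibility of misreading can be claimed.
- **That the Conclusions state a second equivalence objective.** They speak of clinical advantages, which, read with the Discussion, may mean time and speed of response. The sentence still promises a comparison with no comparator behind it.
- **That the historical figures serve the sample size and nothing else.** Strengths and limitations suggests that local and international evidence will help in interpreting the data, so an informal benchmark is signalled. No test, margin or handling of differences between cohorts goes with it. That section concedes the lack of a sham group and of a control for rater expectancy, but does not mention the absent standard-rTMS arm.

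**Conclusion.** The concern stands as a mismatch between the Abstract objective, with its echo in the Conclusions, and everything the trial is designed, analysed and powered to do. The absence of a standard-rTMS arm, a margin and a benchmark test rests on the text alone and needs no assumption.

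The size does rest on assumptions: that the centre's SDs under standard rTMS carry over to aTMS, that r lies between 0 and 0.7, and that the two-sided alpha is 0.05. Under these, an observed mean fall of about 2.0 to 3.3 points with 60 patients, or 3.2 to 5.5 points with 24 completers, would be significant, against 11.3 points with standard rTMS. Success on the primary test would support a fall from baseline and would leave the question of parity open.

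**What to change.** 1. In the Abstract, remove the objective of equal effectiveness with the 4-week course. In the Conclusions, remove the claim of a comparison with the standard protocol.
2. Restate the objectives to match the Methods and Hypothesis: primary, MADRS change from baseline to end of week 3 in the overall sample; second, early versus delayed start; exploratory, left versus right DLPFC aTMS after phase 1.
3. If the centre's historical rTMS results are set beside the trial's, label the comparison descriptive and non-randomised, give a confidence interval, and make no claim of equivalence.

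The cost is wording only. No patients, visits or analyses change, but the claim the trial can make becomes less favourable.

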**Methods:**

A randomized, single-blind, delayed-start trial was planned to commence in Jan 2020. A total of 60 patients will be enrolled from the Institute of Mental Health Singapore within a 2-year period and randomized into the early or delayed-start phase of the trial. The primary outcome of the trial is the improvement of Montgomery-Asberg Depression Rating scale at the end of the active treatment phase.

**Discussion:**

If this study protocol proves to be effective, the findings of this trial will be updated to the College of Psychiatrists, Academy of Medicine Singapore, as well as published in a peer-reviewed journal to enhance local and international TMS treatment guidelines.

**Trial registration:**

ClinicalTrials.gov ID: NCT03941106

## Background

Depression confers a large burden of disease because of its early onset, high prevalence, and the profound disability involved [1]. In Singapore, the lifetime prevalence of depression is 5.8% [2]. The economic burden of depression in the Asia Pacific region [3] and Singapore [4] is high and up to 50% of indirect costs were associated with lost productivity and unemployment. Major depressive disorder (MDD) is a severe mental illness that affects major life domains, such as mental and psychosocial functioning [5, 6]. The current long-term treatment strategies remain suboptimal for patients with MDD. A large proportion of them do not respond satisfactorily to drug therapy and experience relapses over a prolonged period of their life [7, 8].

Electroconvulsive therapy (ECT) is considered to be one of the most effective treatment modalities yielding an 80–90% response rate in patients with the acute phase of depression [9] and 50–70% response rate in patients with treatment-resistant depression (TRD) [10]. Although a highly effective antidepressant treatment, the use of ECT is constrained by stigma and concern over cognitive side effects. Accordingly, great interest has developed in non-invasive brain stimulation (NIBS) therapies such as repetitive transcranial magnetic stimulation (rTMS). These NIBS techniques involve applying a weak electric current/pulse to the brain via an electromagnetic coil to depolarize neurons in targeted cortical regions (most commonly the dorsolateral prefrontal cortex, DLPFC) and thereby modulate mood.

There is now established evidence that rTMS is effective in treating depression [11–13] with approval for its clinical use in countries including the USA, Australia, Singapore, Canada, and Israel. rTMS also has an excellent safety profile, demonstrated in numerous clinical trials, including a substantial number of depressed participants [14]. Most research in rTMS has focused on the pulse frequency [15, 16] stimulation intensity [17] and duration of treatment [18, 19]. rTMS treatment of depression is cost-effective [20] compared to ECT. A local cost-effectiveness study of ECT vs*.* TMS shows that TMS is a highly cost-effective option compared to ECT for non-psychotic depression [21].

Although intermittent theta-burst stimulation (iTBS), a FDA-approved novel form of magnetic stimulation is undergoing intensive study as an alternative approach of rTMS [22–24], the original FDA approved protocol for rTMS, the left 10Hz Dorsolateral Pre-frontal cortex (10Hz L DLPFC) protocol, has a larger evidence base to date. However, there is relatively low efficacy of rTMS compared to ECT [25] and the optimal form of rTMS for patients not responding to initial rTMS modality is unclear [26]. More sessions [27], change of rTMS stimulation intensity [28], change from unilateral to bilateral rTMS treatment [29], or use iTBS to treat drug-resistant depression ([30, 31] have been studied but the results are inconclusive. Current clinical practice commonly changes rTMS modality from high-frequency Left DLFPC (L DLFPC) to low-frequency Right DLPFC (R DLPFC) [32], but there is no evidence that this is more efficacious as compared to adding more sessions of the same rTMS. Moreover, although there is a general acceptance that increased dose and duration of TMS is associated with increased efficacy of rTMS [33], there is preliminary evidence of a delayed response to rTMS [34, 35] suggesting that some patients could be treated effectively with a shorter period of treatment given every weekday, then waiting for several weeks for full clinical improvement from the treatment.

Furthermore, the original FDA-approved protocol for rTMS, which to date has the largest evidence base, is the 10Hz L DLPFC protocol. This involves one session in each working day and patients need to come for the treatment for continuously 4 weeks. For those patients with no or poor response, additional 2 weeks of treatment by rTMS will be supplemented. Therefore, a standard course of unilateral TMS is about 38 min a day for 20–30 working days, substantially limiting the capacity of TMS services to meet the treatment needs of all patients. rTMS requires a considerable time commitment from both patients and clinicians and is of limited utility for patients who do not live within convenient traveling distance from treatment centers. The time needed before treatment response in some patients also makes rTMS unsuitable for some acutely suicidal patients. Accelerating the administration of rTMS (aTMS) by administering multiple sessions of rTMS over a shorter period of time has been shown to potentially be as efficacious as standard rTMS therapy [36–43]. These studies showed that aTMS was safe and efficacious, with no significant side effects reported, with a high level of patient acceptability and significant improvements in subjects’ depression after the aTMS. Thus, aTMS can potentially offer a more cost-effective treatment for depression than standard TMS that can help alleviate the large economic burden of depression by allowing patients to return to their work more rapidly.

## Methods

### Objectives

The primary aim of this study is to test the symptomatic efficacy of aTMS trial protocol. The 2nd aim is to compare the symptomatic efficacy of the early-start aTMS treatment group and delayed-start aTMS treatment group in patients with a DSM 5 Major Depressive Episode. The exploratory aim is to test whether the non-responders to a 1-week course of aTMS will have a higher chance of response to a change in aTMS than repeated the same aTMS modality (from 5 Hz L DLPFC aTMS to 1 Hz R DLPFC aTMS).

### Hypothesis

We hypothesize that accelerated 5 Hz L DLPFC rTMS is effective for the treatment of depressive symptoms with regard to reducing the MADRS scores from baseline to end week 3 in the overall study sample.

### Design of the trial

#### Recruitment and screening

Participants will be recruited from inpatients and outpatients at the Institute of Mental Health (Singapore) by the research team psychiatrists and referrals from other psychiatrists at the Institute of Mental Health.

#### Inclusion criteria

Age ≥21 years.DSM-5 diagnosis of current major depressive disorder.Montgomery-Asberg Depression Rating Scale score of 20 or more.Able to give informed consent.

#### Exclusion criteria

DSM-5 psychotic disorder.Drug or alcohol abuse or dependence (preceding 3 months).Inadequate response to ECT (current episode of depression).Rapid clinical response required, e.g., high suicide risk.Significant neurological disorder, which may pose increased risks with TMS, e.g., epilepsy.Metal in the cranium, skull defects, pacemaker, cochlear implant, medication pump, or other electronic devices.Pregnancy.

The following clinical data will be collected at baseline: age, gender, ethnicity, duration of index episode, type of depression (unipolar/bipolar, melancholic/non-melancholic), number of failed antidepressant treatments, number of previous depressive episodes, age at the first depressive episode, and family history of affective disorder will be noted. Full informed written consent will be obtained from all participants.

#### Randomization at phase 1

In phase 1, subjects were randomly assigned either to the early-start group (immediate active treatment) or the delayed-start group (no TMS treatment for one week followed by active treatment, see Fig. 1). Randomization was done using a random sequence number generator.

